### Statistical analysis plan

The primary variables for the descriptive analyses are records of the incidence of sports-related injuries and illnesses, i.e., recordings of injury or illness events that are conditioned on that the participant is ‘healthy’ at the start of data collection period. Incidences will be calculated separately for injuries and illnesses. The incidence rates will be calculated as the number of new incidents divided by total athlete exposure hours (per 1000 h of sport participation). Health-incidents not related to sport will be analyzed separately. All events will be evaluated according to the mechanism of sports-related injuries and illnesses (independent variables). The data will be assessed for normality and will be presented using quantitative descriptive statistics (mean, median, standard deviation, minimum and maximum for continuous data and frequency and proportion (%) for categorical data). Differences in proportions between different categories (e.g., age-groups, gender, impairments, previous injury, competition frequency and level of severity of impairment) will be analyzed as covariates using chi-square statistics. The primary end point for the injury risk analyses will be time to injury. The incidence data will be further analyzed with the Kaplan-Meier survival analysis method, the log-rank test and Cox proportional hazards regression. To analyze the relationship between training loads and injury and illness incidence, Pearson product moment correlation coefficients will be used. A significance level of 0.05 and 95 % confidence intervals will be used in all tests. The data will be analyzed using IBM SPSS Statistics version 23.

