## Purpose

The purpose here is to present a protocol for a prospective longitudinal study: The Sports-Related Injuries and Illnesses in Paralympic Sport Study (SRIIPSS). In this study we will develop a web-based system that allows self-report data to be collected from Paralympic athletes. Based on these data, we will subsequently: i) record and prospectively estimate the annual incidence of sports-related injuries and illnesses among Swedish Paralympic athletes and ii) explore risk factors and mechanisms for sustaining sports-related injuries and illnesses based on athlete exposure and training loads.

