### Protocol implementation

The SRIIPSS will employ approaches similar to those that have been used in previous sports injury research [9, 23, 30, 33, 52]. It is, however, hypothesized that sports-related injuries and illnesses among Paralympic athletes differ from sport for able-bodied athletes [13, 15]. Existing research has shown that the accessibility, compatibility, interface and design of questions influence the outcome of athletes’ self-report measures [38]. Therefore, we will specifically adapt the protocol to Paralympic sport and thereafter implement the data collection.

For the data recording a commercial product for collection of survey data online (Briteback AB, Norrköping, Sweden; www.briteback.com) will be used. The research team participates in the development of the system to specifically adapt it to, for example, visually impaired athletes. The product enables definition of personal usernames and passwords to protect data from unauthorised use.

A pilot study is planned where we will enroll approximately twenty athletes with different impairments through a convenience sample from the Swedish Paralympic Program. The pilot study aims to evaluate the feasibility of the data collection system, to assure that it works for athletes with physical, visual and intellectual impairments, and to recognize and solve potential problems. The athletes will be asked to fill in the survey during 4 weeks. The pilot study period will end with a cognitive walkthrough to review the primary protocol and also validate the data. This is an evaluation method that aims to assess usability problems of a new tool early in the design process [53]. The athletes and researchers will be asked to evaluate and provide solutions for the proposed system.

Data will be collected from the end of 2016 and continue for approximately 1 year. At the start of the study the athletes fill in baseline information and a psychological profile. The athletes will thereafter be asked to report sports-related injuries and illnesses weekly. The primary outcome of the study is the incidence of injuries and illnesses, divided into a sports-related injury or illness. All data will be based on sport exposure and analyzed for the mechanism of sports-related injuries and illnesses. A closure form will be used when the athlete is back in full training following an injury or illness (Table 2).

**Table 2 Tab2:** Overview of the outcome measures of the SRIIPSS

Outcome measure	Parameter	Measurement

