### Definitions of injury and illness

The main injury definition in the SRIIPSS follows, with some alterations, the definitions previously used for soccer, rugby union, the Olympic Games and athletics [27, 29, 30, 52]:*Any new musculoskeletal pain, feeling or injury that result from participation in Paralympic sport (training or competition) and cause changes in normal training/competition to the mode, duration, intensity or frequency, regardless of whether or not time is lost from training or competition.*

An illness including psychological complaints will be defined as:*Any new illness or psychological complaint that cause changes in normal training/competition to the mode, duration, intensity or frequency, regardless of whether or not time is lost from training or competition.*

The reported incidents will be categorized as ‘sudden onset’ or ‘gradual onset’. A sudden onset incident refers to an incident caused by a specific identifiable episode resulting in a rapid onset of experienced distress. Subsequently, sudden onset injuries will be categorized according to the cause of the incident as: i) traumatic injuries – a condition caused by an identifiable single external transfer of energy (for example, a bone fracture caused by a fall or a ligament tear caused by contact with an obstacle), or ii) overuse injuries – a condition to which no identifiable single external transfer of energy can be associated (examples of overuse sudden onset injuries include tendon tears).

A gradual onset incident refers to a condition that manifests itself over a period of time, or when there is a gradual increase in the intensity of experienced distress, without a single identifiable event being responsible for the condition. Examples of gradual onset conditions include overtraining syndromes and overuse injuries, such as tendinosis and tendinopathies [52].

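### Illness is rated per 1000 hours of sport although its definition does not require a sport cause, so the illness rate is confounded by training volume

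*Protocol article*

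**What the plan says.** The Protocol implementation section gives the primary outcome: "The primary outcome of the study is the incidence of injuries and illnesses, divided into a sports-related injury or illness". The Statistical analysis plan states "Incidences will be calculated separately for injuries and illnesses" and then gives a single formula: "The incidence rates will be calculated as the number of new incidents divided by total athlete exposure hours (per 1000 h of sport participation"). No other denominator is given for illness.

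The two events are defined differently under Definitions of injury and illness. An injury is "Any new musculoskeletal pain, feeling or injury that result from participation in Paralympic sport (training or competition"), so a sport cause is part of the definition. An illness is "Any new illness or psychological complaint that cause changes in normal training/competition to the mode, duration, intensity or frequency". It must affect sport but need not come from it.

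The Statistical analysis plan adds "Health-incidents not related to sport will be analyzed separately", without saying how an illness is assigned to one side or the other. The first aim, under Purpose, is to "prospectively estimate the annual incidence of sports-related injuries and illnesses among Swedish Paralympic athletes". The same analysis section relates training load to injury and illness incidence by Pearson correlation. The Athlete weekly e-diary section computes load as intensity multiplied by duration.

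**The concern.** Hours of sport are a natural denominator for injuries, because the definition ties the risk to time spent in sport. Many illnesses that meet the printed definition, such as an infection caught away from sport, arise with calendar time. Dividing those by training hours gives a number that moves inversely with hours trained.

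Three things are at stake:

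- One of the two primary rates would not be comparable between sports or impairment groups that train for different amounts of time. The Discussion wants exposure-based data to identify higher-risk sports, so such comparisons are likely.
- The load correlation could suggest that high load protects against illness when the pattern is arithmetic.
- The aim of an annual incidence is not met by a rate per hour of sport.

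**Working it through.** The article states no illness rate, training hours or expected precision, so there is no figure to reproduce. All hours, illness rates and spreads below are assumptions.

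**1. Same health, different hours.** Assume 2 illnesses per athlete-year and 52 weeks. Hourly rate = 1000 × illnesses / (hours per week × 52).

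- 6 h/week: 1000 × 2 / 312 = 6.4 per 1000 h
- 18 h/week: 1000 × 2 / 936 = 2.1 per 1000 h

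The ratio is 3.0. In person-time both athletes have 2 per athlete-year, or 1000 × 2 / 365 = 5.5 per 1000 athlete-days, a ratio of 1.0.

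**2. When part of illness does scale with hours.** Let s be the share of illnesses that scales with hours for an athlete training 10 h/week. Expected illnesses are proportional to (1 − s) + s × h/10, and the hourly rate to that quantity divided by h. For 5 against 15 h/week:

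| s | Hourly rate ratio, 5 vs 15 h/week | Person-time rate ratio, 5 vs 15 h/week |
|---|---|---|
| 0% | 3.0 | 1.0 |
| 25% | 2.33 | 0.78 |
| 50% | 1.8 | 0.60 |
| 75% | 1.36 | 0.45 |
| 100% | 1.0 | 0.33 |

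Example at s = 50%: (0.5 + 0.25)/5 = 0.150 and (0.5 + 0.75)/15 = 0.0833; 0.150/0.0833 = 1.8. The hourly ratio is free of distortion only when all illness scales with hours. The person-time ratio describes illness actually experienced per year in every row.

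**3. How much of the hourly rate is hours?** With illness risk and hours independent and log-normal, the share of between-athlete variance in the log hourly rate due to hours is ln(1 + CVh²) / [ln(1 + CVh²) + ln(1 + CVi²)], where CVh and CVi are the coefficients of variation of hours and of illness risk.

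- CVh 0.3, CVi 0.8: 0.086 / (0.086 + 0.495) = 15%
- Equal CVs: 50%
- CVh 0.7, CVi 0.3: 0.399 / (0.399 + 0.086) = 82%

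**4. The load correlation.** On the log scale, load = intensity + hours, and hourly illness rate = illness count − hours (plus a constant). If illness is independent of hours and intensity, and intensity is independent of hours, the covariance of the two is −Var(log hours), which is always negative. A simulation assumed 80 athletes, 2 illnesses per year independent of training, CV of hours 0.3 to 0.7, CV of intensity 0.2, and variance of athlete-level illness risk 0 to 1. Across those settings mean Pearson r was about −0.17 to −0.43, with p < 0.05 in roughly 30% to 100% of runs. Using illness counts over equal follow-up, mean r was about 0 and p < 0.05 in about 5% of runs.

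**The case against.** The strongest defence is that the plan separates incidents unrelated to sport, and that material for sorting them is collected. The Illness report form asks for suspected aetiology, Table 2 lists a closure form with diagnosis and perceived risk factors, and the Injury closure form section describes an expert group that assigns ICD codes to illnesses as well as injuries. This stands in part. A reader might infer that the separation rule cannot be applied to illness at all, and the article does not support that. What it lacks is a stated link from those items to the label sports-related, while its definition admits illness without that label. Even a sorted set is free of distortion only to the extent that its risk truly scales with hours.

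A reader might also infer that the illness rate mainly reflects how little an athlete trains, or that illness is defined with no link to sport. Neither is supported. The variance share in step 3 runs from 15% to 82%, and the definition does require an effect on training or competition; only the causal link is missing. Nor does the article say that athletes with more severe impairment train less.

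Third, the planned category comparisons use chi-square tests on proportions, and the time-to-event analyses use Kaplan-Meier, log-rank and Cox methods. None is stated to use the hourly rate, so it would be wrong to say that those tests are distorted by it. The Pearson analysis refers to incidence without saying in which unit, so that part of the point is conditional.

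Two smaller points also stand. Illness reduces training hours and so the denominator, but injury does the same; losing 2, 5 or 10 of 50 weeks raises an hourly rate by 4%, 11% or 25%. And an hourly rate does not prevent an annual figure from being calculated, since follow-up is about one year; the analysis section simply does not commit to one.

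**Conclusion.** The concern holds in a limited form. The article fixes hours of sport as the only stated denominator for illness, with an illness definition that does not require a sport cause and no printed criterion for sorting. For the part of illness that follows calendar time, the resulting rate is confounded by training volume. At assumed contrasts of 6 vs 18 or 5 vs 15 h/week the spurious ratio is at most 3.0, and it falls to 1.0 if all illness scales with hours. The direction follows from the formula; the actual size cannot be known from the article. If the load correlation uses the hourly rate, the built-in association is negative. The stated annual incidence is a separate, smaller mismatch. The weekly diaries supply the follow-up time needed, so the problem can be corrected at the analysis stage.

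**What to change.** - Keep injury incidence per 1000 h of exposure.
- Make the main illness incidence per 1000 athlete-days, or per athlete-year, of reported follow-up. Keep the hourly illness rate at most as secondary. The athlete-year form also answers the first aim.
- Use the person-time illness rate in the correlation with load and in any comparison of illness rates between sports or impairments.
- State how the suspected-aetiology item already collected determines whether an illness is sports-related, or rename the outcome as illness affecting training or competition.

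The cost is analysis-plan wording; no new data are needed. The downside is that injury and illness rates will no longer share one scale.

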**Fig. 1 Fig1:**
[figure not shown]
Requirements and associations underlying the study protocol for The Sports-Related Injuries and Illnesses in Paralympic Sport Study (SRIIPSS)

The primary requirement of a protocol for longitudinal epidemiological studies in Paralympic sport is to allow prospective studies that cover at least an entire season and include exposure to both training and competition. Second, to reflect the complexity of Paralympic sport, for example pre-existing impairments, use of assistive equipment, pain and other and medical issues, it is required that the design of a surveillance system is specifically adapted to Paralympic sport. Third, to allow the collection of epidemiological data and individual training behaviors, at the same time as there is limited access to coaches and medical personnel, it is advantageous that longitudinal data can be collected online directly from the athletes. There is also increasing evidence that psychological and behavioral factors contribute to the process leading to several sports injuries [50, 51]. Therefore, a psychological profile will be added to identify factors and behaviors related to pain and other activity-limiting sensations [50].

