Baseline data	Gender, age, impairment, sport, training hours, previous injury/illness, medication, aids, anthropometrics, pain	SRIIPSS protocol for baseline data
Psychological profile	Perceived motivational climate	Perceived Motivational Climate in Sport Questionnaire (PMCSQ)
	Active coping	BRIEF COPE
	Body consciousness and body competence	Body Consciousness Questionnaire Scale (BCQ-s)
	Hyperactivity	Diagnostic and Statistical Manual of Mental Disorders (DSM-IV)
	Psychological commitment to exercise	Commitment to Exercise Scale (CTeS)
	General well-being	Likert-scale
Weekly athlete report	Injuries, illnesses, pain, psychological stressors, amount of training and competition, training intensity, sleep	SRIIPSS protocol for weekly athlete data Likert-scale
Injury report	Onset of injury, mechanism of injury, present symptoms, type of injury, impairment-related factors, medical contacts	SRIIPSS protocol for weekly injury data
Illness report	Onset of illness, present symptoms, type of illness, impairment-related factors, medical contacts	SRIIPSS protocol for weekly illness data
Injury/illness closure form	Diagnosis of injury/illness, severity of injury, treatment, perceived risk factors	SRIIPSS protocol for injury/illness closure data

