### Athlete weekly e-diary

To collect data on new sports-related injuries and illnesses as well as on exposure, the athletes will be asked to fill in a weekly e-dairy based on one developed by Jacobsson et al. [33] and adapted for Paralympic sport. Each week, an alert is automatically sent to the participants’ email address and mobile phone, asking them to fill in the weekly questionnaire about their current health status (injuries, illnesses and pain), the amount of training, intensity of training, whether the training is performed at full capacity, competitions, sleep, general well-being and medical contacts. In addition, anxiety/depression and pain/discomfort will be evaluated using two questions from EQ-5D [61].

If the athlete reports a new injury or illness in their weekly e-dairy, a link to an injury or illness report form will be provided, where additional information on the incident are to be reported. The study coordinator (KF) monitors the reported data. If a participant is absent from training because of an undiagnosed injury or illness lasting longer than 3 weeks, the participant will be contacted by phone or email. The athletes will be asked to go through an examination by a sports physician or sports physiotherapist to confirm the clinical diagnosis, in order to validate the data.

Internal training loads will be recorded based on a modified version from Gabbett & Jenkins [62] and Foster et al. [63]. The athletes will be asked to estimate their total rating of perceived exertion (RPE) during the past week on a 0–10 point RPE-scale [62]. Previous research has demonstrated that the RPE method is a valid method to quantify exercise training during a wide variety of exercise types [63], and the method has also been shown to provide valid estimates when compared to heart rate and blood lactate concentration. The training load will be calculated by multiplying the training session intensity with the duration of the training during the week and will be further analysed with the relationship of injury/illness, acute loads and chronic loads [43, 62, 64].

Assistance will be provided, if necessary, for athletes with vision or intellectual impairment, or severe physical impairment. At the start of the study the athletes will be educated about the importance of monitoring. Feedback will be given, if desired, to allow data to be used to the athletes’ benefit.

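### Weekly load as worded leaves out competition hours, and the only stated incidence rate pools training and competition

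*Protocol article*

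**What the plan says.** **Exposure.** Study design and rationale requires the study to "cover at least an entire season and include exposure to both training and competition". Table 2 (under Protocol implementation) lists the weekly report as covering "amount of training and competition, training intensity, sleep", so both amounts are collected.

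**Load.** Athlete weekly e-diary asks athletes to "estimate their total rating of perceived exertion (RPE) during the past week on a 0–10 point RPE-scale". Load is then obtained by "multiplying the training session intensity with the duration of the training during the week" and is to be examined as acute and chronic load against injury and illness. The Statistical analysis plan correlates load with injury and illness incidence using Pearson coefficients.

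**Numerator.** Under Definitions of injury and illness, an injury must "result from participation in Paralympic sport (training or competition", so events in either setting count.

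**Rate.** The Statistical analysis plan gives one rate, computed separately for injuries and illnesses and expressed per 1000 hours: "number of new incidents divided by total athlete exposure hours". It states no split by setting. Competition frequency appears only as one of the categories compared by chi-square tests of proportions.

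**Intended use.** The Discussion wants exposure-based data to show which sports carry more risk. Definitions of injury and illness also foresees comparison with earlier studies, and Sports injury research (Background) says that most of these recorded injuries in competition only.

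**The concern.** There are two separate issues.

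The first is a measurement rule. The article treats training and competition as distinct throughout, and its load formula names only training. Competition hours are therefore missing from the explanatory variable, while competition injuries are present in the outcome. The error is not uniform, because it grows with the hours spent competing. A proportionate understatement that was the same in every week and athlete would leave a Pearson coefficient and an acute-to-chronic ratio unchanged. One that varies with the competition calendar can distort both.

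The second is interpretability. A pooled rate is an average of the two setting-specific rates, weighted by hours. If those rates differ, two sports with identical risk in each setting but different calendars will show different pooled rates. A ranking of sports, or a comparison with a rate observed in competition only, would then partly describe how much time is spent competing.

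**Working it through.** The article states no rate, event count or load value, so there is no figure to reproduce. All numerical inputs below are assumptions, and only the formulas come from the article.

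**1. Load.** Let T be training hours, C competition hours and R the weekly exertion rating.

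- Load as worded: T × R.
- Load with all sport hours: (T + C) × R.
- Fraction lost for a given R: C / (T + C).

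Assumed usual week: 10 h training, no competition, R = 5, so load = 10 × 5 = 50.

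| Assumed week | As worded | All hours | Lost |
|---|---|---|---|
| T = 4, C = 4, R = 7 | 4 × 7 = 28 (0.56 of usual) | 8 × 7 = 56 (1.12) | 4/8 = 50% |
| T = 6, C = 2, R = 6 | 6 × 6 = 36 (0.72) | 8 × 6 = 48 (0.96) | 2/8 = 25% |
| T = 8, C = 2, R = 6 | 8 × 6 = 48 (0.96) | 10 × 6 = 60 (1.20) | 2/10 = 20% |

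The understatement occurs in every row. Its size depends on competition hours. How low the week looks against a usual week depends on how far training is cut: 0.56 in the first row, 0.96 in the third.

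These figures let R reflect competition effort, as a total weekly rating may. If R reflected training alone (R = 5), the first row as worded would be 4 × 5 = 20. The offset from the weekly rating is therefore 28 − 20 = 8, against a shortfall of 56 − 20 = 36.

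**2. Pooled rate.** Let f be the competition share of hours and k the ratio of the competition rate to the training rate. Relative to the training rate, the pooled rate is (1 − f) + f × k. Take two groups with the same risks in each setting and assumed shares of 5% and 15%.

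| k | f = 0.05 | f = 0.15 | Ratio |
|---|---|---|---|
| 1 | 0.95 + 0.05 = 1.00 | 0.85 + 0.15 = 1.00 | 1.00 |
| 3 | 0.95 + 0.15 = 1.10 | 0.85 + 0.45 = 1.30 | 1.18 |
| 5 | 0.95 + 0.25 = 1.20 | 0.85 + 0.75 = 1.60 | 1.33 |
| 8 | 0.95 + 0.40 = 1.35 | 0.85 + 1.20 = 2.05 | 1.52 |

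Wider assumed shares (2% and 20%) give ratios of 1.00, 1.18, 1.67 and 2.37 at k = 1, 2, 5 and 10. Shares of 2% and 10% give 1.00, 1.08, 1.30 and 1.61. There is no distortion at k = 1. Setting-specific rates do not depend on f, and they are also what would show whether k differs from 1.

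**The case against.** **The pooled rate does not contradict the design.** This stands. The denominator covers both kinds of exposure and matches the numerator, and the first aim is an annual incidence, which an overall rate estimates. A reader might infer that the rate breaches the requirement to "include exposure to both training and competition". It does not. The article also never says that no other rate will be reported, and a fuller plan may add some. The gap concerns the comparisons the article announces, and the chi-square test on competition frequency does not fill it, because that test does not adjust a rate for competition share.

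**Load does not ignore competition altogether.** This also stands. A reader might infer that competition effort counts as zero load. The rating covers the whole past week and is not restricted to training, so competition effort may raise the multiplier. Only competition duration is left out. Training could have been meant loosely, but the same section and Table 2 name competition separately, so that is not the natural reading.

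**Competition weeks need not look like low-load weeks.** A reader might infer that they do, and that the analysis is thereby pushed towards finding low load harmful. The first inference needs a marked cut in training hours in those weeks; the second also needs a higher injury rate in competition. The article states neither.

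**The size of the rate effect is assumed.** The article gives no competition share and no rate ratio between settings, so it does not support a statement that groups competing more will show higher rates.

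**Setting cannot be assigned to every event.** Gradual-onset injuries are defined as having no single responsible event, and illnesses need no sporting cause. For these, total hours are a defensible denominator. This limits the fix to sudden-onset injuries.

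**Conclusion.** The load point holds on the wording. The formula omits competition hours that are collected every week, so load is understated in weeks with competition. The fraction lost is C / (T + C), which is 20% to 50% in the assumed examples, partly offset if the weekly rating reflects competition. The direction of any resulting bias in the correlation cannot be derived from the article.

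The rate point is conditional. The pooled rate is valid as an overall summary. It misleads in comparisons only if both the setting-specific rates and the competition shares differ. With assumed shares of 5% and 15%, the ratio of pooled rates runs from 1.00 (equal rates) to 1.52 (competition rate 8 times the training rate). The change is worth making because the article plans exactly such comparisons and already collects the hours.

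**What to change.** 1. In Athlete weekly e-diary, define weekly load as the weekly exertion rating multiplied by training plus competition duration, and say that the rating covers both. This costs one sentence, and the data are already collected.
2. In the Statistical analysis plan, keep the overall rate per 1000 hours for all incidents. For sudden-onset injuries, also report rates per 1000 training hours and per 1000 competition hours.
3. Check that the injury form records whether a sudden-onset injury occurred in training or competition. The listed items do not name the setting explicitly, although the mechanism item may capture it and the full form is not shown. If it is absent, add one item before data collection.
4. Do not force gradual-onset injuries or illnesses into a setting. Report them over total hours only.

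The main cost is precision. With about 100 athletes spread over many sports, competition rates will have wide intervals and will be sparse by sport, so they should be presented as estimates with intervals alongside the overall rate.

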### Setting and participants

Potential participants will be recruited through the Swedish Paralympic Program, which covers candidates for the Summer and Winter Paralympic Games. The total number of athletes in the Swedish Paralympic program is around 100. All potential participants will be invited by post or email. They will receive information about the proposed study, a request for a contact e-mail and phone number, a consent form for participation and a prepaid return envelope. To be eligible for the study the athlete should belong to one of the ten eligible impairment types, according to the IPC classification system, and participate in either a Paralympic summer or winter sport (Table 1). The following inclusion criteria will be used: age 18–55 years, being a registered athlete within the Swedish Paralympic Program, being able to communicate in Swedish and having the opportunity to respond weekly to a web-based questionnaire. As the number of Swedish Paralympic athletes is small and this is an understudied topic, a total population design will be applied.

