### Outcome measures

#### Baseline data

Baseline data will be collected using a web-based questionnaire including: i) participant characteristics (i.e., gender, age, height and weight); ii) demographic data; iii) impairment characteristics (i.e., type of impairment, use of assistant devises, medications); and iv) sport characteristics (i.e., type of sport, preconditions, hours per week involved in training and competition). The athletes will also be asked about existing injuries, illnesses and pain. In addition, women will be asked about menstruation and use of contraceptives.

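### The only stated analysis of age is a chi-square comparison of age-groups; age in years, in the Cox regression already planned, would use the data better at almost no cost

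*Protocol article*

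**What the plan says.** All places are in the protocol article.

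- **Statistical analysis plan:** "Differences in proportions between different categories (e.g., age-groups, gender, impairments" and further factors "will be analyzed as covariates using chi-square statistics". Neither the number of age-groups nor the version of the test (Pearson or trend) is given. The level is fixed: "A significance level of 0.05".
- **Same section:** the end point of the injury risk analyses is time to injury, with Kaplan-Meier, log-rank and Cox regression. How age enters the Cox model is not stated.
- **Baseline data:** the questionnaire covers "i) participant characteristics (i.e., gender, age, height and weight" among other items. The format of the age item is not stated.
- **Setting and participants:** eligibility is "age 18–55 years", so age is very probably known in years. "The total number of athletes in the Swedish Paralympic program is around 100", and the whole population is to be invited because of this: "As the number of Swedish Paralympic athletes is small".

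**The concern.** Age-groups is the only form in which the plan names age for analysis. Two kinds of information can be lost. Grouping treats all athletes within a group as the same age. With three or more groups, an ordinary Pearson chi-square also ignores that the groups have an order, and spreads a trend over several degrees of freedom.

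Exploring risk factors is the study's second aim. The number of athletes is capped by the size of the national programme, so power lost through the form of a variable cannot be regained by recruiting more. A better form is available from data already planned, in a model already planned.

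**Working it through.** The article states no power, effect size, injured proportion or number of age-groups, so there is no figure of its own to reproduce. The check asks how much power grouping costs on the same injured yes/no outcome. This isolates the grouping from the choice of outcome.

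**Inputs from the article:** level 0.05 (two-sided assumed); at most about 100 athletes; ages 18 to 55.

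**Assumed inputs:** 50% or 70% injured; odds ratio 1.8 per standard deviation of age; age uniform or normal; two, three or four groups of equal size; a monotone effect, linear on the log-odds scale.

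**Step 1: formula.** A 1-df test on continuous age with a given power has noncentrality λ = (1.960 + z_power)². At 80% power, λ = (1.960 + 0.842)² = 7.85. At 70% power, λ = 6.17. Cutting age into k equal-size groups keeps a share of λ. For uniform age the share is 1 − 1/k², that is 0.750, 0.889 and 0.9375 for k = 2, 3 and 4. For normal age it is the mean of the squared group means of a standard normal, that is 0.637, 0.793 and 0.861. Power of the Pearson test then comes from the noncentral chi-square distribution with k − 1 degrees of freedom.

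| Power with continuous age | Age distribution | 2 groups | 3 groups | 4 groups |
|---|---|---|---|---|
| 80% | uniform | 67.9% | 65.4% | 61.4% |
| 80% | normal | 60.9% | 60.1% | 57.3% |
| 70% | uniform | 57.6% | 54.4% | 50.2% |
| 70% | normal | 50.9% | 49.5% | 46.5% |

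The loss runs from 12.1 points (80% row, uniform, two groups) to 23.5 points (70% row, normal, four groups).

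**Step 2: where the loss comes from.** Ignoring order alone, with no grouping loss, takes 80% down to 70.9% with three groups and 64.5% with four: 9.1 and 15.5 points. With two groups there is no order to lose, and the whole loss comes from dichotomising.

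**Step 3: simulation, n = 100, 4000 replicates, quantile groups.** Ranges cover uniform and normal age.

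| Injured | Continuous | 2 groups | 3 groups | 4 groups |
|---|---|---|---|---|
| 70% | 72–73% | 53–59% | 52–57% | 48–52% |
| 50% | 80–82% | 63–70% | 57–65% | 57–62% |

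The loss is about 11 to 24 points, in line with step 1. Size under the null was 4.5 to 5.1%. A 1-df trend test on the same three or four groups had 62 to 70% at 70% injured, so it recovers much of the loss.

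**Step 4: fewer athletes.** With 70 athletes, 60% injured, log-odds 0.6 per standard deviation, uniform age and equal-width groups, continuous age had 66 to 68%. Pearson had 54%, 50% and 45% on two, three and four groups. The loss is similar, from a lower starting point.

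**Step 5: when the effect is not monotone.** Under a U-shaped age effect a linear term had about 4% power, no better than the level of the test, against 28 to 38% for chi-square on three or four groups. These values depend on the U assumed, but the direction does not.

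**Step 6: price of guarding against step 5.** A joint 2-df test of a linear and a quadratic term, when the effect is in truth linear, has 70.9% where the 1-df test has 80%, and 59.7% where it has 70%. Against the Pearson figures in step 1, the net gain is 70.9 − 67.9 = 3.0 to 70.9 − 57.3 = 13.6 points in the 80% rows. In the 70% rows it is 59.7 − 57.6 = 2.1 to 59.7 − 46.5 = 13.2 points.

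**The case against.** The strongest reply is that the chi-square comparison is not the risk analysis. The section moves from descriptive statistics to comparisons of proportions, and then names time to injury as the end point for injury risk, with Cox regression. A reader might infer that the study's whole assessment of age suffers the loss above. The text does not support that, because nothing says age is grouped in the Cox model. For the same reason no power loss can be charged to the Cox analysis. This part of the reply stands and limits the point to the chi-square comparison.

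Other parts also stand:

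- Chi-square statistics could include a trend test. That the test ignores order is the usual reading, not a stated fact. Age in years is likewise inferred from the eligibility range.
- A reader might fault the absence of cut-points. A condensed article may leave these to a fuller plan, so their absence is no finding.
- Severity of impairment appears in the same list, and a reader might want a trend test there too. The article shows no ordered severity scale across its ten impairment types, so a trend test may have no meaning.
- Age is one example in a list, the aim is exploratory and no hypothesis about age is stated.
- A linear effect is the best case for a linear term. Step 5 shows that the comparison reverses for a U-shape.

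What the reply does not remove is that grouped age with chi-square is a stated choice, the only one made for age, and that a more efficient use of the same data is open at no cost in data collection.

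**Conclusion.** The point holds as a low-priority improvement. If a Pearson chi-square on two to four age-groups is used, power for a monotone age effect is about 11 to 24 points lower than with continuous age. This assumes 100 athletes, 50 to 70% injured, an odds ratio of 1.8 per standard deviation, and uniform or normal age. None of these except the approximate number of athletes is in the article, so the range is conditional and is not a property of the plan. Ignored order explains it only in part: with two groups the loss is due to dichotomising alone. If the fix includes a joint test that also detects curvature, the net gain for a linear effect is smaller, about 2 to 14 points on the yes/no outcome, in exchange for protection against a U-shape.

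**What to change.** In the Statistical analysis plan section, state that inference on age rests on age in years in the planned Cox regression. Prespecify a non-linear term (quadratic or spline) and test it jointly with the linear term. Keep age-groups for descriptive tables. Where a category with a defined order is compared by proportions, name a 1-df trend test; leave categories without a defined order under the ordinary chi-square.

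The cost is a change of wording. No new data are needed, provided the baseline item records age in years or date of birth, which should be confirmed. The statistical price is one extra degree of freedom for a quadratic term (a spline may need more). The alternative is a linear term alone, which rests on a linearity assumption and would miss a U-shaped effect.
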